**Figure 3: Serum biomarkers and depression: Relationship of depression at baseline and outcome.**

Our second example from the IBS study involves an examination of a particular subgroup within the sample. Seventeen percent of our IBS patients were under anti-depression treatment. We found increased baseline levels of BDNF in those patients (p=0.0058), which remained unaltered during placebo treatment (Figure 3). Experiments conducted in mice have shown that a genetic variant of BDNF (V66M) plays a key role in genetic predisposition to anxiety and depressive disorders (58). A recent meta-analysis of 11 studies comparing depressed and non-depressed studies confirmed that BDNF serum levels were lower in depressed volunteers (72). Moreover, analysis of additional 8 studies showed that BDNF levels are elevated following a course of antidepressant treatment (72), consistent with the findings of the present study. Remarkably, clinical depression was not correlated with any of our primary endpoints.

A secondary aim of the GWI project is to better define and describe this complex disease and explore potential mechanisms of healing. This can include biological changes as well as psychosocial changes. The PI of this project has worked on multiple projects to set up study designs to gather and analyze data to describe multi-level health changes. This builds on other work linking biological changes to perceived stress, other psychosocial and physical symptom changes (20,56,57). To better understand GWI, we will use validated instruments to collect information on baseline and study-related changes that may occur in the volunteers’: 1) biology, such as inflammatory cytokines associated with GWI manifestation (10,2) psychosocial attitudes and functioning such as perceived social support and improvements in social functioning, 3) symptomatology such as medical history and other symptoms. Correlations between disease factors (such as main GWI symptom) and treatment factors (such as specific acupuncture diagnosis and practitioners’ prognosis for each case) will also be considered in order to understand how acupuncture might work in the treatment of GWI. Last, toward the aim of better understanding this disease and its treatment, correlational analyses of symptom expression and treatment effectiveness by socioeconomic status, ethnicity, race, and co-morbidities will also be conducted.

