Our treatment protocol is based on a published effective protocols in similar disease (eg 76) as well as clinical experience. Due to the individualized nature of the treatments, systematic detailed records will be kept by practitioners of each treatment visit including: symptom presentation and consequent diagnosis, dose of acupuncture (measured as number of needles used and techniques applied), prognosis following that treatment. Additional clinical observations will be solicited qualitatively using an open response question format. This information is critical to best understand how acupuncture might be work and how the most effective treatment schedules can be designed. This treatment level data will also be examined for trends to better understand which specific types of treatment are most effective in the treatment of GWI.

This study has the potential to find an effective treatment for GWI that is safe and easy to administer. Multiple clinical studies have shown acupuncture to be safe, effective, and cost effective. Our study design allows us to gather specific treatment evidence applicable to the entire population of individuals with GWI. This study is also designed to gather data on the mechanisms of healing in GWI and of acupuncture; this information can be generalized toward the development of treatments of other diseases and disorders associated with military service, improving the health and quality of life of service men as well as veterans. This is an important consideration as use of Veterans Affairs mental health services have greatly increased, by Persian Gulf-era veterans, and also returning Iraq/Afghanistan veterans as well as Vietnam era veterans (71). Acupuncture has the potential to be an effective, safe, low-cost treatment option which could be of help to all of these populations.

7. Objectives/Specific Aims/Study Questions.

Objectives: To find a successful treatment for GWI, by gathering data to better understand: 1) the effectiveness of acupuncture in treating GWI; 2) the mechanisms of this disease.

Specific Aim: In a sample of veterans with GWI, evaluate the effectiveness of an individualized acupuncture treatment protocol on the volunteers’ most distressing GWI symptom.

8. Study Design.

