We will utilize an unblinded randomized controlled trial design with a wait-list-control. A simple random sample will be used to obtain our sample from the accessible population. Volunteers will be randomly assigned to treatment or wait list arm using computer assignment.

Our primary outcome is quality of life. In an effort to better understand this disease and its treatment we are considering psychosocial variables (quality of life, depression, anxiety, mood), fatigue, sleep quality, and pain. All of the measurement instruments used in this trial have been used before and published on in peer reviewed scientific journals. All have shown good validity and reliability. Details of the measures are listed below in item “15. Study Procedures/Study Interventions**”.**

9. Study Population.

The study results will be generalizable to individuals with Gulf War Illness as determined by responses on the Gulf War Illness Symptom Checklist, who live within 90 miles of the Boston area and meet the inclusion/exclusion criteria as listed in “item 10 Inclusion/Exclusion Criteria” below. Participants will not be excluded due to age, race, ethnicity, or sex limitations.

Our study team has successfully recruited volunteers to acupuncture trials in populations with other complex diseases such as Irritable Bowel Syndrome (43), and Chronic Pelvic Pain (93), and in challenging populations such as a pediatric population (93). Based on our experience from other trials (18) we expect to screen four volunteers for every one that is enrolled.

As described in section “C. Advertisements, Posters, and Press Releases to Recruit Volunteers” we will be using two forms of recruitment; from the Gulf War Registry and by advertisement. The combination of these two techniques will promote timely recruitment and accrual.

10. Inclusion/Exclusion Criteria.

Inclusion:

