For our calculations, we will use the normal distribution assumption and explore this using a normal plot and goodness of fit test. If violations are found, non-parametric tests or transformations will be utilized. Variance equivalence will be tested using the F-test. Our protocol is designed to assure sample independence and adherence will be closely monitored. Before beginning the main statistical analyses, baseline variable levels across groups will first be considered to assess group equivalence. If the groups are not balanced on any baseline characteristics, these factors will be considered as variables in later multi-variate regressions.

The Centers for Disease Control defines Gulf War Illness (GWI) or Complex Multisymtom Illness (CMI) as the presence for at least 6 months of one or more self-reported symptoms from at least two clusters of symptoms: Cluster A (fatigability), Cluster B (Mood and Cognition), Cluster C (Musculoskeletal) (10). A single measure of severity that addresses all possible presentations of GWI does not exist. Thus we chose to use as the main outcome a general measure of health. Our primary outcome, the SF-36 (53) is a 36-item measure of global health. It is well recognized with good reliability and validity. Items address multiple aspects of physical and mental health as well as functionality. Eexperience to date from nearly 400 randomized controlled clinical trials suggests that the SF-36 is also a useful tool for evaluating the benefits of alternative treatments (88).

Comparisons between the treatment and wait-list groups will be based on improvement in SF-36 scores. We are considering the primary outcome to be the Physical Component Summary score of the SF-36. We chose to use the SF-36 in order to show general health related quality of life in this population with very diverse complaints. The Physical component subscale was chosen because it focuses on 2 of the three Centers for Disease Control GWI clusters (fatigue and musculosketal complaints). Statistically we will test mean differences between groups following 2 months of treatment using Student’s t-tests at an alpha=0.05. Analyses of secondary outcomes will include a test for mean differences between groups using student’s t-tests at an alpha=0.05.

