The SF-36 is a multi-purpose, 36 item health survey. It yields an 8-scale profile of functional health and well-being scores as well as psychometrically-based physical and mental health summary measures and a preference-based health utility index. It is a generic measure, as opposed to one that targets a specific age, disease, or treatment group. Accordingly, the SF-36 has proven useful in surveys of general and specific populations, comparing the relative burden of diseases, and in differentiating the health benefits produced by a wide range of different treatments (53).

The 16 item Multidimensional Assessment of Fatigue (MAF) scale measures four dimensions of fatigue: severity (#1-2), distress (#3), degree of interference in activities of daily living (#4-14), and timing (#15-16). Fourteen items contain numerical rating scales (#1-14) and two items have multiple-choice responses (#15-16). Respondents are asked to reflect over the past week. The MAF is a revision of the Piper Fatigue Scale, a 41-item measure of fatigue developed for research purposes and tested with oncology patients (68,85).

The Profile of Mood States (POMS) assessment has been used since1971 to measure of mood states and their fluctuations in ill and healthy populations. The POMS Standard assessment is a factor-analytically derived inventory that measures six identifiable mood or affective states. It shows good reliability, validity, and usability (61)

The Pittsburg Sleep Quality Index is a well-used and validated scale that measures various qualities of the subject’s sleep. It has shown good reliability (34).

The Measure Your Medical Outcomes Profile is a three item measure that allows participants to name their main complaints and rate the severity of them over time (40l).

The Beck Anxiety Inventory (BAI) measures the severity of anxiety in adults and adolescents. This 21 item measure can be self-administered and evaluates both physiological and cognitive symptoms of anxiety and item overlap with other self report depression inventories is minimized. Each item is descriptive of a symptom of anxiety and is rated on a scale of 0 to 3. It shows good reliability and validity (63).

The McGill Pain scale is perhaps the most recognized and utilized pain measurement device across a range of ailments. This 15 item measure asks participants to describe the quality of their pain using various different descriptors (55).

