## ****The Carroll Depression scale is a 21 item scale which asks respondents to endorse multiple facets of depression. We have used this in our previous work and are impressed with its performance. It has good reliability and validity. (14,28).****

The study also includes a 6-month follow-up at which time the treatment group will have received 2-months of bi-weekly treatment and 4 months of weekly treatment. This treatment dose was determined from previous studies and the clinical experience of our team. The wait-list group members will have received 2 months of study attention while they served as the control component of the design. These wait list members then receive 4 months of weekly of courtesy acupuncture. Due to the unbalanced treatment schedule across the wait list and treatment groups they are not directly comparable. Yet preliminary data can be attained from each of the groups using within-groups comparisons, and student’s t-test comparisons of means. For example, changes in the wait-list scores from the main outcome timepoint (2 months) to 6 months can inform future trials considering necessary dose of treatments by highlighting the effects of weekly treatment. In this same way, we may find that while the active treatment group received more frequent sessions during the first 2 months of treatment, the 4 months of weekly treatment carry benefit as well.

19. Data Management:

Methods used for data collection:

To maintain patient confidentiality, study staff will maintain 3 databases. The first will be used for screening and patient communication only and will include necessary patient contact information. The second database will be used to maintain scores on study instruments and will not contain identifying information. A third database will be maintained to track the acupuncture treatments by volunteer identification number and will also contain no identifying information.

Data collection forms are listed in section “B. Surveys, Questionnaires, and Other Data Collection Instruments”. Our main outcome is the physical component of the Sf-36 (53).

Confidentiality:

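### The single Specific Aim (the volunteer's most distressing symptom) is not what the primary test of SF-36 PCS at 2 months measures, and no section links the two

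*Protocol*

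**What the plan says.** Section 7 sets a two-part Objective, to understand "1) the effectiveness of acupuncture in treating GWI; 2) the mechanisms of this disease". Below it stands one Specific Aim: to "evaluate the effectiveness of an individualized acupuncture treatment protocol on the volunteers’ most distressing GWI symptom". The background (section 6) adds a descriptive aim: "A secondary aim of the GWI project is to better define and describe this complex disease and explore potential mechanisms of healing".

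The primary outcome is described in several places:

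- Section 8: "Our primary outcome is quality of life".
- Section 12: the sample size uses the SF-36 PCS, with SD 20, a difference of 7 points and 60 per group.
- Section 18: "We are considering the primary outcome to be the Physical Component Summary score of the SF-36". The between-group t-test is at 2 months with alpha 0.05. PCS was chosen because "it focuses on 2 of the three Centers for Disease Control GWI clusters", namely fatigue and musculoskeletal complaints.
- Section 19: the SF-36 physical component is named, without qualification, as the main outcome.

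Section 18 also describes a patient-nominated instrument: "The Measure Your Medical Outcomes Profile is a three item measure that allows participants to name their main complaints" and rate their severity over time. Section B lists it at baseline, endpoint and follow-up. Secondary outcomes get between-group t-tests at alpha 0.05.

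**The concern.** A Specific Aim tells the reader what the main result will establish. Here the aim concerns the one symptom each volunteer finds worst, while the main result will be a mean difference in a generic physical health summary. The two can diverge. A volunteer whose worst complaint is low mood, poor concentration or trouble getting to sleep could improve on that complaint with little change in PCS. A volunteer could also gain on PCS while the worst complaint stays as it was.

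What is at stake is interpretation. If the aim stands as written, a PCS result in either direction invites a conclusion about the most distressing symptom that the primary analysis cannot carry. The analysis that could carry it is not identified as the one that answers the aim.

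**Working it through.** The point rests mainly on comparing texts.

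**Step 1. What the aim requires, and what each measure supplies**

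| Requirement of the aim (section 7) | SF-36 PCS (sections 12, 18, 19) | MYMOP (section 18, section B) |
|---|---|---|
| Volunteer's own worst symptom is identified | No; same items for everyone | Yes; volunteer names main complaints |
| That symptom is scored over time | No; physical summary score | Yes; severity rated over time |
| Every symptom cluster can count | Focus on 2 of 3 clusters | Yes; content chosen by the volunteer |
| Measured at baseline and 2 months | Yes | Yes |
| Trial sized on it | Yes | No |
| Primary | Yes | No |

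**Step 2. The omitted cluster is part of eligibility.** Section 10 counts mood, cognition and sleep-onset complaints among the qualifying symptoms. A worst symptom in that cluster is therefore expected in this population. PCS, on the protocol's own reasoning, does not focus on it.

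**Step 3. Search for a link.** Section 18 explains why a general measure was used: no one severity scale covers all presentations of GWI. It explains PCS by cluster coverage. It also says that a tailored measure lets volunteers report on the symptoms that matter most to them. No section says which of these analyses answers the Specific Aim. MYMOP is one of ten entries listed beside the SF-36 in section B. The analyses that section 18 names by cluster use other scales and are within-group.

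**Step 4. The plan's own figure.** The only power statement, 80%, concerns PCS. Inputs from section 12 are n = 60 per group, difference 7 and SD 20. Two-sided alpha of 0.05 is assumed, as sidedness is not stated.

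Power = Φ(7 / (20·√(2/60)) − 1.96) = Φ(7/3.651 − 1.96) = Φ(−0.043) = 48%

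One-sided, the power is 61%. The stated 80% is not reproduced. That is a separate matter and this point does not depend on it.

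**Step 5. What the same sample could show on the aim itself.** The protocol gives no SD or target difference for MYMOP, so only SD units are possible. With 60 per group, two-sided alpha 0.05 and 80% power, the detectable effect is

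√(2/60)·(1.96 + 0.84) = 0.51 SD

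| Assumed MYMOP effect (SD units) | Power at 60 per group | n per group for 80% |
|---|---|---|
| 0.35 | 48% | 129 |
| 0.50 | 78% | 63 |
| 0.60 | 91% | 44 |

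The worst-symptom question can be answered usefully from the planned sample if the effect is about half an SD or more. These figures ignore any gain from baseline adjustment.

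**The case against.** The strongest reply is that this is a defensible design described loosely: a generic primary outcome for a varied illness, with a patient-nominated secondary. Much of that stands.

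- PCS bears on the Objective of effectiveness in GWI, so a reader who infers that the primary test misses the trial's whole question goes too far. It misses the Specific Aim.
- The aim is not untested. MYMOP falls under the between-group secondary t-tests.
- A reader might infer from the tentative verb in section 18 and the phrase in section 8 that the primary outcome can be chosen after the fact. The documents do not support this. Section 12 sizes the trial on PCS, section 19 names it outright, and section 18 fixes the test, alpha and timepoint. Quality of life is the construct that the SF-36 was chosen to represent.
- Section 15 has the acupuncturist identify the most distressing symptom at the first session, and wait-list volunteers have no session before 2 months. That is no flaw in the comparison: the identification serves diagnosis and treatment, and no section uses it as an outcome.
- Mood and cognition supplies most of the symptom lines in section 10. Counting lines does not show how many volunteers have their worst symptom there.
- One could model dilution. If one third had no PCS gain and the rest gained 7 points, the mean would be 7 × 2/3 = 4.7. The zero gain has no source. Section 10, read literally, asks for a severe symptom in each cluster, so those volunteers may gain on PCS too.

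Ranking of secondaries and testing order may properly sit in a statistical analysis plan. What does not stand is the idea that the stated reason for PCS settles the matter. It justifies a general measure, but it does not connect that measure to the Specific Aim.

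**Conclusion.** The mismatch is real and stands in the current text. Section 7's only Specific Aim is the volunteer's most distressing symptom. The sized and tested primary outcome is PCS at 2 months, which neither identifies nor scores that symptom and, by the protocol's own account, does not focus on one of the three clusters. The primary test does not answer the Specific Aim. It does bear on the broader Objective, and MYMOP addresses the aim as an unranked secondary.

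The effect on the result cannot be put into a number. It depends on how many volunteers have their worst symptom in mood or cognition and how their PCS responds, and the protocol gives neither. The conclusion needs no such figure, because it rests on the wording of sections 7, 8, 12, 18 and 19. It should be corrected, since it governs what the trial may claim about its stated aim. It does not invalidate PCS as a primary outcome.

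**What to change.** 1. **Section 7:** reword the Specific Aim so that its primary test is SF-36 PCS at 2 months, acupuncture against wait-list.
2. **Sections 8 and 18:** say the same. Specify quality of life in section 8 as PCS, and replace the tentative wording in section 18 with a plain statement that PCS is the primary outcome.
3. **Section 18:** name the main symptom nominated on MYMOP at baseline, in both arms, as the secondary outcome that answers the worst-symptom question. Rate that same symptom at 2 months and compare arms with adjustment for its baseline score.
4. **Interpretation:** state that no confirmatory claim about the most distressing symptom will rest on the PCS result.

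The alternative is to keep the aim and make the MYMOP symptom primary. That would need a new sample size with an SD and target difference for MYMOP, which the protocol does not contain.

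The cost of the recommended change is a few sentences, with no new data, visits or volunteers. The downside is that the sponsor's headline aim becomes narrower: physical health-related quality of life in place of the symptom that matters most to each volunteer.
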